# Improving the accuracy and efficacy of diagnosing polycystic ovary syndrome by integrating metabolomics with clinical characteristics: study protocol for a randomized controlled trial

**DOI:** 10.1186/s13063-020-4060-6

**Published:** 2020-02-11

**Keywords:** Polycystic ovary syndrome, Metabolomics, Clinical signs and symptoms, Accuracy and efficacy

## Abstract

**Background:**

Polycystic ovary syndrome (PCOS) is a complex endocrine syndrome with poorly understood mechanisms. To provide patients with PCOS with individualized therapy, it is critical to precisely diagnose the phenotypes of the disease. However, the criteria for diagnosing the different phenotypes are mostly based on symptoms, physical examination and laboratory results. This study aims to compare the accuracy and efficacy of diagnosing PCOS by integrating metabolomic markers with common clinical characteristics.

**Methods:**

This is a prospective, multicenter, analyst-blinded, randomized controlled trial. Participants will be grouped into (1) people without PCOS (healthy control group), (2) patients diagnosed with PCOS based on clinical indices (experimental group 1), and (3) patients diagnosed with PCOS based on metabolomic indices (experimental group 2). A total of 276 participants, including 60 healthy people and 216 patients with PCOS, will be recruited. The 216 patients with PCOS will be randomly assigned to the two experimental groups in a 1:1 ratio, and each group will receive a different 6-month treatment. The primary outcome for the experimental groups will be the effect of PCOS treatment.

**Discussion:**

The results of this trial should help to determine whether using metabolomic indices is more accurate and effective than using clinical characteristics in diagnosing the phenotypes of PCOS. The results could provide a solid foundation for the accurate diagnosis of different PCOS subgroups and for future research on individualized PCOS therapy.

**Trial registration:**

Chinese Clinical Trial Registry, ID: ChiCTR-INR-1800016346. Registered 26 May 2018.

## Background

Polycystic ovary syndrome (PCOS) is a complex endocrine syndrome [1, 2] that exhibits chronic ovulatory disorders, hyperandrogenism, insulin resistance, and metabolic disorders [3]. PCOS has a prevalence of 5%–10% globally [4, 5], and it is one of the most common endocrine and metabolic disorders in Chinese women. PCOS is strongly associated with insulin resistance and dyslipidemia, which affect patients with obesity, type 2 diabetes, and metabolic syndrome (MetS) [6–10]. Evidence also suggests that patients with PCOS may have a higher prevalence of asthma [11], nonalcoholic fatty liver disease [12], and mental disorders [13] such as depression and anxiety [14]. However, the underlying mechanisms of PCOS are still poorly understood, making clinical diagnosis and treatment very difficult.

To determine whether a patient has PCOS, careful assessment of hyperandrogenism, hyperandrogenemia, ovulatory function, and ovarian morphology is required. The recent diagnostic criteria for PCOS are mostly based on a combination of other criteria/statements that are still disputed, and because of the different clinical manifestations and complex pathogenesis of the disease, the criteria are mainly aimed at ruling out other diseases. The accuracy of the diagnosis and the evaluation methods for assessing the individual criteria is even more critical.

PCOS has diverse phenotypes [15–17] and thus requires individualized treatment. The European Society of Endocrinology [2] proposed four phenotypes, including a type without hyperandrogenemia. When diagnosing the disease, it was suggested that abnormalities in steroidogenic enzymes, prolactin excess, and thyroid problems need to be ruled out. In China, the classification of subtypes and treatment of PCOS are mainly based on clinical indices, such as sex hormones (e.g., follicle-stimulating hormone (FSH), luteinizing hormone (LH), LH/FSH ratio, free testosterone, dehydroepiandrosterone (DHEAS), androstenedione, sex-hormone-binding globulin), serum lipids (e.g., total cholesterol, triglycerides, low-density lipoprotein cholesterol (LDL-C), high-density lipoprotein cholesterol (HDL-C), apolipoprotein (Apo) A, Apo B), and the results of oral glucose tolerance tests and immunoreactive trypsinogen tests [1]. This heterogeneity in diagnostic criteria could significantly lead to misdiagnoses. Therefore, it is urgent to explore a new detection method to standardize the classification of phenotypes and establish an efficient diagnostic and treatment strategy for PCOS. The development and application of new technologies, such as genomics, proteomics, and metabolomics, provide a new direction for diagnosing PCOS phenotypes. However, in genomics, although the findings of genome-wide association studies have implications, the direct pathogenic gene for PCOS has not been found yet. In proteomics, some scholars have identified potential biomarkers for PCOS phenotyping, but their clinical application is limited because proteins, or amino acids, are highly susceptible to interference, which can bias the results. Lastly, due to the high sensitivity and specificity of metabolomic methods, it can be assumed that some metabolic markers can be used to distinguish whether patients with PCOS have high androgen levels.

In the attempt to classify PCOS phenotypes, recent studies have adopted various measurements such as nuclear magnetic resonance [18], liquid chromatography/mass spectrometry [19], and others [20, 21]. In our previous study [3], using ultra-high-performance liquid chromatography/quadrupole time-of-flight mass spectrometry, we found two subgroups of patients with PCOS: one with hormone metabolism disorders and the other with lipid metabolism disorders.

This trial aims to compare the accuracy and efficacy between using metabolomic indices and using clinical characteristics in diagnosing PCOS phenotypes. Our findings could provide a basis for further research on individualized PCOS therapy.

## Methods

### Study design

This is a prospective, multicenter, analyst-blinded, randomized controlled trial. Subjects will be grouped into one healthy control group and two parallel experiment arms, as follows: (1) people without PCOS (healthy control group), (2) patients diagnosed with PCOS based on clinical indices (experimental group 1), and (3) patients diagnosed with PCOS based on metabolomic indices (experimental group 2). A total of 276 participants, including 60 people without PCOS and 216 patients with PCOS, will be recruited. The 216 patients with PCOS will be randomly assigned to the two experimental (diagnosis) groups in a 1:1 ratio. After group assignment, medical detection results, relative information, and biological samples will be collected from all three groups. Additionally, the blood samples from all participants will be tested using metabolomic methods for further study, while the analysis results will be totally blinded to all participants and their research physicians. Based on our previous study [3], we will categorize patients with PCOS into two subgroups: patients with hormone metabolism disorders (subgroup 1) and patients with lipid metabolism disorders (subgroup 2).

The two diagnosis groups will be automatically divided into the two different subgroups according to patient characteristics. The main difference is that in group 1, diagnosis will be based on clinical indices [1], such as clinical signs and symptoms and ultrasonography findings, while in group 2, diagnosis will be based on metabolomic indicators. All patients will receive treatment according to their subtype group, and the treatment will consist of Diane-35 or metformin. The intervention period for all experimental groups will be 6 months, and the results will be evaluated after the completion of three constant treatment sessions (3 months).

Outcomes will be assessed, and the data will be analyzed by someone blinded to the assignment of participants. The study design is shown in Fig. 1, and the timeline is presented in Figs. 2 and 3.

**Fig. 1 Fig1:**
[figure not shown]
Flow chart diagram showing the summary of the trial design

**Fig. 2 Fig2:**
[figure not shown]
Timeline of the the trial

**Fig. 3 Fig3:**
[figure not shown]
The schedule of forms and procedures, according to the Protocol Items. Physical examination includes: ultrasonography of bilateral ovarian anad clinical biochemical indicators. Clinical biochemical indicators routine urine tests, routine blood tests, liver function, pregnancy tests, LH/FSH ratio, sex hormone related indicators blood lipid related indicators and endocrine related indicators. There are twenty-five clinical biochemical indexes including eight sex hormone-related indexes: FSH, LH, PRL, E2, P, Ts, AMH, AND vitD; nine blood lipid indicators: TC, TG, HDL, LDL, ApoA1, Apo B, Lp(a), FFA, hsCRP; seven endocrine-related indicators: GLU (0h, 30min, 120min), INS (0h, 30min, 120min), BUA. The main elevation index was LH/FSh ratio. Note: ultrasonography examination is scheduled for the 14th day of menstruation, if the patient with rare ovulation has follicular diameter > 10mn or luteal appearance, should be reviewed in the subsequent menstrual cycle. Unmarried women without sexual life suggested abdominal B ultra. All blood samples will be collected on an empty stomach within 72 hours from the first day of menstruation

The main treatment center will be the Department of Endocrinology and Metabolism of the Affiliated Wuxi People’s Hospital of Nanjing Medical University, which will enroll 60 participants for the healthy control group and 108 participants who, in the experimental group (108/216), will be randomly assigned between the two experimental groups. Two other treatments centers—Wuxi Maternal and Child Health Centers Clinical Hospital and Jiangyin People’s Hospital—will enroll the other 108 participants, who will also be randomly assigned between the two experimental groups.

### Participants and recruitment

People without PCOS will be enrolled in the healthy control group only if they do not have any other disorders that may influence sex-related hormones and metabolic conditions. For the experimental groups, PCOS will be diagnosed according to the 2018 Chinese Endocrine Society clinical practice consensus on PCOS [1], which is based on the widely accepted criteria for PCOS published by Rotterdam [22, 23]. Patients who are of reproductive age and can follow the procedure, including strict contraception for 6 months, will be informed of this trial. If a potential participant expresses interest, a face-to-face interview regarding the entire trial process will be conducted in a reception room in the three hospitals. Patients who meet the inclusion criteria will be enrolled if they provide written informed consent. Potential participants will be recruited in two ways: (1) the experimental group participants will be recruited by approaching patients with PCOS who are admitted to an outpatient department or inpatient ward of each center; the official microblog and WeChat platforms of each center will also be used; and (2) the healthy control group participants will be directly recruited by approaching volunteers in the health examination center of Wuxi People’s Hospital.

### Inclusion criteria

Participants who meet all of the following criteria will be enrolled in the experimental groups:
Diagnosed with PCOS according to the 2018 Chinese Endocrine Society clinical practice consensus, i.e., presence of at least two of the following three conditions, excluding other etiologies: (a) clinical or biochemical hyperandrogenism, (b) oligo-anovulation (menstrual cycle length of > 35 days and having eight or fewer menstrual cycles per year), and (c) a polycystic ovarian morphology characterized by at least 25 small follicles (2–9 mm) in the entire ovary and/or an increase in ovarian volume of ≥ 10 mLA reproductive woman aged 18–45 yearsAble and willing to comply with the interventions and follow-up evaluations

### Exclusion criteria

The exclusion criteria are as follows:
Currently receiving treatment in another experimental study or having just finished a trial in the past 30 daysTreated with Diane-35, metformin, or other forms of estrogen, progesterone, and lipid-regulating and hypoglycemic drugs (e.g., glucocorticoids, spironolactone, antibiotics, bacterial regulators, anti-inflammatory drugs) within the past 12 weeksAn allergy or intolerance to Diane-35, metformin, or any of its componentsPresence of congenital adrenal cortical hyperplasia, hypercorticism, androgen-secreting tumors, Cushing’s syndrome, thyroid dysfunction, gonadotropin deficiency, hyperprolactinemia, premature ovarian insufficiency, functional hypothalamic amenorrhea, or diabetesA medical history of malignant tumors, particularly a history of surgery, radiation, or chemotherapy for a gynecological malignant tumorPresence of liver dysfunction (alanine aminotransferase and aspartate transaminase levels > 1.5-times the normal values) or chronic liver diseasePresence of hematopenia or thrombotic diseaseIs pregnant or expects to be pregnant during the studyHas an unstable medical, physical, or mental statusHas a medical history of symptomatic ventricular arrhythmias with torsion ventricular tachycardia (torsade de points)Unable to complete the procedures of the studyAny other situation that would interfere with the study evaluation, procedures, or completion

### Subject dropout

Subject dropout occurs when:
The subject quits the studySafety issues arise (e.g., adverse events (AEs), failure of contraceptive measures, accidents)The subject is lost to follow-upResearchers remove the subject from the trial due to poor compliance, severe liver dysfunction, complications, or serious AEs

### Suspension of the trial

The trial may be suspended if the following events occur:
A significant safety problem is found, such as serious impairment of the patients’ liver function or the sudden onset of other life-threatening illnesses. In this case, the trial will be suspended, and the participants will have to undergo medical treatment until recoveryThe diagnostic and therapeutic effects are poor, such as no improvement in menstrual/metabolic disorders (to be evaluated at the third month of therapy). In this case, the researchers will evaluate the physical condition of the participants and decide whether to suspend the trial if necessaryA major mistake (e.g., patients taking the wrong doses, patients taking or using medicine without following the physician’s advice) is made that will affect the results of the trialThere is a major problem in funding or management, such as withdrawal of funding, which can cause the trial to be discontinued early

### Randomization

The Department of Good Clinical Practice of Wuxi People’s Hospital will lead the randomization process by using a random number generator in the Statistical Package for Social Sciences (SPSS) version 21.0 (SPSS Inc., Chicago, IL, USA).

Random sequences will be placed in opaque envelopes, numbered in order, and then sent to a clinical researcher and physicians.

The envelopes will be opened sequentially to decide upon the allocation of participants. In this trial, the physicians and trial participants will be blinded to the group assignment.

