### Blinding

In the experimental groups, participants will not be informed of the group assignment, the type of diagnosis, or the treatment that they will receive. Data managers and the statistician will also be blinded. Only the trial administrator (a steering committee of the Department of Good Clinical Practice, Wuxi People’s Hospital), who will be responsible for assigning the participants into different subgroups and monitoring the entire trial process, will be not blinded. Moreover, the clinical research physicians will be blinded to the assignment of group 1, whose treatment will be decided based on their clinical practice, while they will have access to the diagnostic and treatment allocation data for group 2. The clinical physicians will be responsible for learning how to use the blinding method to communicate with the participants to ensure diagnosis and treatment blinding. The blinding procedure will be conducted until the data are locked and the trial is completed. Unblinding will only be permitted in case of a medical emergency or when a participant quits the trial. All cases of unblinding will be documented.

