#### Metabolomic index group

Most of the interventions for the metabolomic index group will be similar to those for the clinical index group. The main difference is that the division of the subgroups will be based on metabolomic indices. The physicians in this group will be informed of the allocation of participants to the subgroups and will provide the corresponding treatment scheme to all participants. The physicians will not be allowed to change the scheme during the trial and will remain blinded to the metabolomic results to minimize the possibility of any influence on treatment decisions.

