### Data collection and monitoring

Data on basic patient characteristics will be collected and recorded by screeners when participants are recruited. Clinical signs and symptoms, physical examination findings, metabolomic evaluation results, short- and long-term outcomes, assessment of diagnosis accuracy and treatment efficiency, and details of the AEs will be recorded by trial assessors and clinical researchers in case report forms (CRFs).

Completed CRFs will be checked and reviewed by a five-person steering committee, which is composed of two supervisors of the major trial center, a data statistician, and two data administrators. The committees are completely independent from the research team and will be constantly blinded to the group allocation.

All data entry and management procedures will be conducted in an OpenClinica System (version 3.12) database. The committee members will need to be qualified in data analysis and will have been trained uniformly.

To ensure the accuracy of data, two data administrators will independently perform data entry and validation. Any issues with the information in the CRFs will be reported by the data administrators to the steering committee. Any revisions will be modified by the administrators according to feedback from the committee. Once the accuracy of data is confirmed, the electronic database will be locked while real-time tracking and monitoring will remain open.

The steering committee and the Department of Good Clinical Practice in Wuxi People’s Hospital will monitor the entire trial (e.g., checking the progress of recruitment, participant data including CRFs, the protocols for researchers, informed consent forms, and any other study-specific files) and audit the trial conduct at least once a month.

All information will be made available to the investigators whose proposed use of the data has been approved by the relevant committee for up to 15 years following publication. The findings will be presented at conferences and published in peer-reviewed journals. A summary of the findings will be provided to the participants upon request via telephone.

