To further investigate the findings of this trial, we will conduct a prospective cohort study, expanding the sample size of patients with PCOS and analyzing the detection frequencies. This study is a multicenter, randomized, open-label, blinded clinical study aiming to standardize the diagnostic classification and treatment of PCOS. The sensitivity and specificity of integrating metabolomic indices in the diagnostic criteria will be compared with diagnosing the disease with clinical indices alone. Our findings may help improve the empirical classification, find predictive biomarkers, and assist in establishing an integrated biomarker system for developing precise diagnostic and treatment strategies for different PCOS subgroups in the future.

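### Treating physicians are declared blinded to group assignment, but the plan's own procedures reveal every patient's arm to them

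*Protocol article*

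**What the plan says.** All places are in the protocol article.

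- **Randomization** makes the claim without qualification: "In this trial, the physicians and trial participants will be blinded to the group assignment". The same section says of the envelopes: "Random sequences will be placed in opaque envelopes, numbered in order, and then sent to a clinical researcher and physicians". They are opened in sequence; who opens them is not stated.
- **Blinding** says the clinical research physicians are blinded to group 1, whose treatment they decide from their own practice, but that "they will have access to the diagnostic and treatment allocation data for group 2".
- **Metabolomic index group** says physicians are told which subgroup each participant falls in, stay blinded to the metabolomic results, and are bound by this rule: "The physicians will not be allowed to change the scheme during the trial". **Clinical index group** contains no such rule.
- **Study limitations** says the group 1 diagnosis is made by several physicians, with a three-physician team for undecided cases.
- **Blinding** names one unblinded party, a trial administrator described as a steering committee of the Good Clinical Practice department, "who will be responsible for assigning the participants into different subgroups and monitoring the entire trial process, will be not blinded". **Data collection and monitoring** describes a five-person steering committee that includes a statistician and two data administrators, and adds: "The committees are completely independent from the research team and will be constantly blinded to the group allocation".
- **Study design** and the abstract call the trial analyst-blinded. The **Discussion** says: "This study is a multicenter, randomized, open-label, blinded clinical study".

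**The concern.** The trial compares two ways of subtyping PCOS, each leading to one of the same two drugs. A difference between arms can be credited to the subtyping method only if patients are otherwise handled alike. Physician blinding is one safeguard for that, and the article claims it.

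If physicians know the arm, expectation can affect how they counsel and follow patients, and how readily they keep them in the trial. Retention matters because researchers may remove a participant for poor compliance (Subject dropout), and because the full analysis set drops anyone who misses the primary outcome evaluation (Statistical analyses). A reader who relied on the stated blinding would discount these routes when interpreting the result.

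**Working it through.** No arithmetic applies beyond counting. The check sets the statements side by side.

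**1. Can physicians be blinded to arm?**
- There are two randomized arms, 1:1, 108 + 108 = 216 patients (Study design; Sample size calculation).
- Group 2: the physician is handed the subtype and the treatment that follows from it (Blinding; Metabolomic index group).
- Group 1: the physician makes the subtype diagnosis and decides treatment (Blinding; Study limitations).
- A physician given the subtype is treating a group 2 patient; one who must determine it is treating a group 1 patient. With no third randomized arm, knowing one group identifies the other. Blinding to group 1 alone is therefore not possible.
- The result is the same whether one set of physicians serves both arms or each arm has its own. It covers 216 of 216 planned patients.
- What remains is blinding to the metabolomic results, stated for both arms and consistent with the procedures.

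**2. Envelopes.** They go to a clinical researcher and to the physicians whom the same section calls blinded. That contradicts the claim and leaves custody with clinical staff. It does not show that anyone learns an assignment before enrolment.

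**3. Steering committee.** The same label is attached to a body that is unblinded and assigns subgroups, and to one that is blinded throughout. If they are one body, the statistician and data administrators sit on an unblinded committee, although the Blinding section also says that data managers and the statistician are blinded. If they are two bodies, the text does not separate them.

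**4. Treatment changes.** The bar on altering the scheme is written for group 2 only, while group 1 treatment follows the physicians' practice. Who decides the subtype is the intended contrast. Whether treatment may be altered afterwards is a separate matter, and the text does not make it equal across arms.

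**5. Participants.** The Blinding section says they are not told which treatment they receive. The Clinical index group section describes one drug taken for 21 days with a 7-day pause and another taken every day. A participant can see the difference. It identifies the drug, not the arm, because both drugs are used in both arms.

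**6. Effect on outcomes.** The main index is the LH/FSH ratio, a laboratory measure, and Study design has outcomes assessed and analysed by someone blinded. Detection bias on it is therefore limited. Care and retention remain exposed.

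**The case against.** The best defence of the claim is that the unblinded administrator assigns subgroups, so physicians might simply receive a subgroup for every patient and be unable to tell the arms apart. The Blinding and Study limitations sections rule this out, because in group 1 the physicians themselves diagnose and choose treatment.

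Other objections have force and limit what can be said:

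- **Concealment.** A reader might infer that physicians can foresee allocation. The document does not support this: the sequence is computer-generated, and the envelopes are opaque, numbered and opened in order. Knowing the arm after opening is different from foreseeing it.
- **Baseline after randomization.** Study design says: "After group assignment, medical detection results, relative information, and biological samples will be collected from all three groups". This might suggest that baseline data follow randomization. But the sentence includes the healthy controls, who are not randomized; eligibility already requires assessment of androgen status, cycles and ovarian morphology; and screeners record basic characteristics at recruitment.
- **Participants' knowledge of arm.** The visible schedules might suggest that self-reported symptoms at weeks 30 to 41 are unblinded. They are not shown to be: recognising the drug does not reveal the arm, and an outcome assessor makes those calls. Leakage through physicians is possible but not documented.
- **Committees.** Two bodies may be meant. The monitoring section speaks of committees in the plural and lists the steering committee and the department separately. Ambiguity is established; access of a blinded committee to the allocation is not.
- **Freedom in group 1.** This is partly inferred from silence. The article calls the interventions mostly similar and bans other PCOS treatments in both arms.

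The analyst-blinded label is compatible with unblinded physicians, and credibility tests are planned at weeks 15, 26 and 41. Neither makes the unqualified statement about physicians true.

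**Conclusion.** Wrong as written. The statement that physicians are blinded to group assignment describes a property that the design does not have. Treating physicians know the arm of every patient, 216 as planned, and are blinded only to the metabolomic results. This rests on one assumption: that a physician knows whether a subtype was supplied or had to be decided.

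The bias cannot be quantified from the document. It would act mainly through care and retention, and only to a limited degree through measurement of the LH/FSH ratio. Three lesser points accompany it: concealment is at risk and inconsistent with the stated blinding; the steering committee's status is at least ambiguous; and care may differ between arms beyond the subtyping method. The document does not support concluding that concealment failed or that participants know their arm.

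**What to change.** - State that treating physicians are unblinded to arm and blinded only to the metabolomic results. Limit the blinding claim to laboratory, outcome assessors, data managers and statistician, and correct the combined open-label and blinded description in the Discussion.
- Qualify the statement that participants do not know their treatment, since the schedules differ visibly.
- Name the unblinded administrator and the blinded case-report-form review committee as separate bodies with separate members.
- Reconcile the Blinding, Clinical index group and Metabolomic index group sections on whether treatment may be changed. Which rule applies is for the clinicians.
- For any participant still to be randomized, have the Good Clinical Practice department hold the envelopes and release each one only after eligibility, baseline data and the clinical subtype are recorded.
- Trial status reports recruitment completed in August 2019 but also mentions a screening phase. If allocation is complete, the envelope change no longer applies; correct the claims and report the lack of physician blinding as a limitation when interpreting results.

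The cost is wording and, where still possible, a change of envelope custody. The downside is a less favourable stated level of blinding.
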